# Preoperative versus postoperative ultrasound-guided rectus sheath block for improving pain, sleep quality and cytokine levels of patients with open midline incisions undergoing transabdominal gynaecological operation: study protocol for a randomised controlled trial

**DOI:** 10.1186/s13063-015-1096-0

**Published:** 2015-12-10

**Keywords:** Pain, Rectus sheath block, Sleep, Cytokines

## Abstract

**Background:**

Rectus sheath block (RSB) is used for postoperative pain relief in patients undergoing abdominal surgery with midline incision. Preoperative RSB has been shown to be effective, but it has not been compared with postoperative RSB. The aim of the present study is to evaluate postoperative pain, sleep quality and changes in the cytokine levels of patients undergoing gynaecological surgery with RSB performed preoperatively versus postoperatively.

**Methods/Design:**

This study is a prospective, randomised, controlled (randomised, parallel group, concealed allocation), single-blinded trial. All patients undergoing transabdominal gynaecological surgery will be randomised 1:1 to the treatment intervention with general anaesthesia as an adjunct to preoperative or postoperative RSB. The objective of the trial is to evaluate postoperative pain, sleep quality and changes in the cytokine levels of patients undergoing gynaecological surgery with RSB performed preoperatively (*n* = 32) versus postoperatively (*n* = 32). All of the patients, irrespective of group allocation, will receive patient-controlled intravenous analgesia (PCIA) with oxycodone.

The primary objective is to compare the interval between leaving the post-anaesthesia care unit and receiving the first PCIA bolus injection on the first postoperative night between patients who receive preoperative versus postoperative RSB. The secondary objectives will be to compare (1) cumulative oxycodone consumption at 24 hours after surgery; (2) postoperative sleep quality, as measured using a BIS-Vista monitor during the first night after surgery; and (3) cytokine levels (interleukin-1, interleukin-6, tumour necrosis factor-α and interferon-γ) during surgery and at 24 and 48 hours postoperatively.

**Discussion:**

Clinical experience has suggested that RSB is a very effective postoperative analgesic technique, and we will answer the following questions with this trial. Do preoperative block and postoperative block have the same duration of analgesic effects? Can postoperative block extend the analgesic time? The results of this study could have actual clinical applications that could help to reduce postoperative pain and shorten hospital stays.

**Trial registration:**

Current Controlled Trials NCT02477098 15 June 2015.

## Background

Multimodal analgesia techniques can be used to provide adequate analgesia for abdominal surgery with midline incision, with the goal of limiting postoperative pain. Each new technique must meet increasing demands for safety and effectiveness. Pain after abdominal surgery has two components, somatic and visceral, both of which are initiated by nociceptor stimulation [1].

Reliance on high-dose opiates to obtain adequate postoperative analgesia has been strongly associated with postoperative nausea and vomiting, sedation and ileus [2, 3], all of which can delay postoperative recovery. Epidural analgesia (EA) has been reported to result in complications such as nerve injury, epidural haematoma and low blood pressure [4]. Additionally, some patients are unsuitable for EA, such as those with coagulopathy and sepsis, those with limited movement and those who are uncooperative [5]. Further, the high reported failure rate cannot be ignored [6]. Transversus abdominis plane (TAP) block has become popular in recent years. However, there is no guarantee of satisfactory block for midline incision [7, 8].

Rectus sheath block (RSB) was first introduced into clinical practice in 1899; as described by Schleich, it is a regional anaesthetic technique that involves blocking of the ventral rami of the 7th to 12th intercostal nerves by injection of local anaesthetic into the space between the rectus muscle and posterior rectus sheath to achieve analgesic effects [9, 10]. With the development of long-acting local anaesthetic agents and ultrasonic technology, RSB has become safer and more effective [11, 12]. Recently, it has been widely used for postoperative analgesia, including that after laparoscopy, umbilical hernia repair, paediatric surgery and gynaecological surgery [13–17]. However, better analgesic effects can be achieved when incisions are limited to the midline, and RSB only provides analgesia for somatic pain but does nothing to alleviate pain of visceral origin [18].

An early finding that less oxycodone than morphine is needed for visceral pain relief after major abdominal surgery [19] has been confirmed in patients undergoing laparoscopic gynaecological surgery [20]. Oxycodone is a semisynthetic thebaine derivative μ-opioid receptor agonist that has been in clinical use since 1917, and it has been the most commonly used analgesic in Finland for the management of postoperative and other acute pain in adults since the 1960s [21]. Over the past two decades, the use of oxycodone has surpassed that of morphine in several countries [22].

In our recent clinical observation, the combination of RSB and patient-controlled intravenous analgesia (PCIA) with oxycodone has been shown to be a potentially better multimodal analgesic technique for patients undergoing transabdominal gynaecological surgery with open midline incision. Thus, this combination treatment might alleviate both somatic and visceral pain. However, it is unknown how this technique influences postoperative sleep quality and cytokine levels.

During the first postoperative nights, sleep patterns can be severely disturbed, with marked decreases in total sleep time, slow-wave sleep duration, and rapid eye movement sleep, which are features associated with frequent sleep arousals [23–29]. The pronounced reduction in sleep during the first nights following major surgery can affect recovery [30]. Sleep disturbance after surgery can be caused by factors such as the anaesthesia used, the environment after surgery, pain and sympathetic activation, and psychological responses [24]. Sound sleep impacts adaptive immune functions. Specifically, the acute effects of regular sleep have been shown to have lasting influences on cytokine levels compared with 24 hours of continuous wakefulness [31–33]. Surgical stress accompanied by general anaesthesia is believed to suppress immunity, and surgery can influence the levels of secreted cytokines, which are responsible for suppressing cell-mediated immunity after surgery [34]. In addition, anaesthetics and sedative agents themselves are known to have immunomodulatory activities [35]. However, little information is available about the use of regional block as an RSB adjunct in addition to the effects of oxycodone on sleep quality and immune function during the immediate postoperative period.

RSB is usually performed before surgery because it inhibits reflection of the skin incision and reduces the amount of intraoperative anaesthetic used [36–38]. While postoperative surgical RSB appears to provide effective postoperative analgesia for patients undergoing major gynaecological surgery [39], there have been no randomised, controlled trials comparing the differences in immune function of patients receiving RSB before versus after surgery.

We hypothesised that performing RSB after surgery might result in a longer duration of analgesic effects and have a subtle influence on sleep quality after surgery but that it will not decrease the perioperative cytokine levels of patients undergoing gynaecological surgery. The present report will follow the guidelines of the Standard Protocol Items: Recommendations for Interventional Trials (SPIRIT).

## Methods/Design

### Study design and outcomes

This study is a prospective, randomised, controlled (randomised, parallel group, concealed allocation), single-blinded trial. All patients undergoing transabdominal gynaecological surgery will be randomised 1:1 to the treatment intervention with RSB preoperatively or postoperatively. The objective of the trial is to evaluate the postoperative pain, sleep quality and changes in cytokine levels of patients undergoing gynaecological surgery with RSB performed preoperatively versus postoperatively.

The primary objective is to compare the interval between leaving the post-anaesthesia care unit (PACU) and receiving the first PCIA bolus injection on the first postoperative night between patients who receive preoperative RSB and those who receive postoperative RSB. The secondary objectives will be to compare the following: (1) cumulative oxycodone consumption at 24 hours after surgery between patients who receive preoperative versus postoperative RSB; (2) postoperative sleep quality, which will be measured using a bispectral index (BIS)-Vista monitor during the first night after surgery [40, 41]; and (3) cytokine levels (interleukin-6 (IL-6), tumour necrosis factor-α (TNF-α), IL-1 and interferon-γ (IFN-γ)), which will be compared during the operation and at 24 and 48 hours postoperatively.

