#### General anaesthesia

General anaesthesia will be induced as follows: 2 mg/kg propofol given intravenously (IV); 2 mg midazolam given IV; 0.4 μg/kg sufentanil given IV; and 0.2 mg/kg cisatracurium given IV. The patient’s lungs will be ventilated with intermittent positive pressure. The tidal volume will be adjusted to 6–8 ml/kg, and the ventilator rate will be adjusted to maintain end-tidal CO_2_ at 35–45 mmHg. For maintenance of anaesthesia, sevoflurane (Baxter Healthcare of Puerto Rico, Guayama, Puerto Rico) will be used at an end-tidal concentration of 2–2.5 %, and an air-oxygen (FiO_2_: 50 %) mixture will be adjusted for the maintenance of anaesthesia with intraoperative titration of sufentanil given IV, according to a BIS value of 40 to 60, after intubation in both groups. A 0.05 mg/kg dose of additional cisatracurium will be applied if needed. At the end of surgery, the trachea will be extubated after the return of spontaneous respiration and neuromuscular function, and the patient will then be transferred to the PACU. The patients will receive pain relief (visual analogue scale, VAS, score of less than 3) using 5–10 μg titrated sufentanil. Three millilitres of venous blood will be collected for plasma inflammatory cytokine measurements at the PACU.

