#### RSB technique

Before surgery (Group PRE) or at the end of surgery (Group POST), a bilateral single-shot RSB will be performed under ultrasound guidance by one anaesthesiologist. The rectus muscle will be imaged with an ultrasound probe in the transverse orientation at the level of the umbilicus. A broadband (5–12 MHz) linear array ultrasound probe (S-Nerve Ultrasound System, Sonosite, Bothell, Washington, USA) will be used with an imaging depth of 4–6 cm. A PAJUNK (PAJUNK, GmbH, Medizintechnologie, Geisingen, Germany) insulated needle (50-mm, 21-gauge) will be introduced a few millimetres from the probe using an in-plane technique at an angle of approximately 45° to the skin. The ultrasound imaging will allow for identification of the rectus muscle and two hyperechoic railway-like lines deep in this muscle (the posterior rectus sheath and peritoneum). Under direct vision, the needle tip will be advanced to the desired position, where 20 ml of 0.5 % ropivacaine hydrochloride will be injected, causing hydrodissection of the rectus muscle away from the posterior rectus sheath. The technique will be repeated on the opposite side. It will be performed by one investigator using a completely aseptic technique.

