## Discussion

Clinical experience has suggested that RSB is a very effective postoperative analgesic technique, and we will answer the following questions with this trial.

Do preoperative block and postoperative block have the same duration of analgesic effects? Can postoperative block extend the analgesic time? In theory, a single dose of local anaesthetic usually has a maximum duration of 12 hours [9], and if we delay the timing of the block, it should extend the duration of action after surgery. However, we must consider the original anatomical structures that are changed by surgery and whether these changes will alter the effects of block. To address this problem, we will compare the analgesic effects of PCIA, which will provide specific analgesia for both visceral and somatic pain after surgery in both groups. The indicators that we will record will include the time to administration of first rescue opiate and the number of self-controls.

The results of this study could have actual clinical applications that could help to reduce postoperative pain and shorten hospital stays. In addition, the increasing number of operations performed requires the rapid and accurate delivery of regional block anaesthesia. If good results can be obtained with postoperative block, then we can perform it at the PACU after surgery to speed up the operation flow. To minimise the imbalance of anaesthesiologists and gynaecologists, the same group of gynaecologists will perform the standard surgical procedures, and all anaesthesia will be administered by one anaesthesiologist. The limitation of our study is that we will evaluate only a single-dose RSB because a continuous infusion catheter cannot be used due to the current technical level and higher cost. However, it could be attempted in future studies.

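### The primary interval compares two block-timing strategies on opioid-free time after the PACU; it cannot show whether the two blocks last equally long, and it leaves out rescue opioid given in the PACU

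*Protocol article*

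**What the plan says.** As its main aim, the Study design and outcomes section sets out to "compare the interval between leaving the post-anaesthesia care unit (PACU) and receiving the first PCIA bolus injection", with the night after surgery as the window. The Abstract and the Sample size section use the same interval.

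The arms differ in when the block is placed (RSB technique): "Before surgery (Group PRE) or at the end of surgery (Group POST), a bilateral single-shot RSB will be performed".

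The Background hypothesis is that "performing RSB after surgery might result in a longer duration of analgesic effects". The Discussion asks two questions. The first is "Do preoperative block and postoperative block have the same duration of analgesic effects"; the second is "Can postoperative block extend the analgesic time". It then gives the timing rationale, "if we delay the timing of the block, it should extend the duration of action after surgery", and a separate influence: "we must consider the original anatomical structures that are changed by surgery and whether these changes will alter the effects of block". It presents the PCIA comparison as the way to address this, and lists the time until a first rescue opioid among the indicators to be recorded.

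The General anaesthesia section states that patients get pain relief to a VAS below 3 "using 5–10 μg titrated sufentanil". That sentence stands between the transfer to the PACU and the blood sample taken there, so this opioid comes before the primary clock starts.

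**The concern.** The first Discussion question, and the hypothesis if read as a property of the block, are about how long each block works once placed. The only analgesic interval defined starts at PACU exit. By then the PRE block has been running through the whole operation and the POST block has only recently been given. The interval therefore combines two things: the later placement of the POST block, and any change in how the block performs in tissue that has been operated on. The Discussion names both but has no outcome that separates them.

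The start point raises a second issue. PACU exit is a post-randomisation event that pain itself may delay, and it follows opioid titration. A patient whose block fails early can be treated with sufentanil, leave the PACU comfortable and enter the primary analysis at time zero with no rescue counted.

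What is at stake is the interpretation of a positive result. Read through the Background hypothesis, a longer POST interval could be taken as evidence that the block itself lasts longer when given after surgery. The design cannot show that.

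**Working it through.** **Inputs**
- Pilot means of the primary interval (Sample size): PRE 203.2 min, POST 258.2 min.
- Block times (RSB technique): PRE before surgery, POST at its end.
- Operating time: no mean is given. Patients with operations over 3 hours (180 min) are removed (Criteria for removal from the study).
- Assumed: g, the gap between the two block times relative to the operation, is about the length of surgery. Also assumed: e, the mean time from the POST block (or, in PRE, the matching point at the end of surgery) to PACU exit, is the same in both arms.

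**Step 1: the plan's own difference.** 258.2 − 203.2 = 55.0 min in favour of POST.

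**Step 2: what the interval contains.** Let D be the time from block to first PCIA bolus in each arm.
- PRE interval = D(PRE) − g − e
- POST interval = D(POST) − e
- POST minus PRE = [D(POST) − D(PRE)] + g

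If the first bolus came when the block wore off and both blocks lasted equally long, the bracket would be zero and the interval would still favour POST by g. One observed number cannot be split into the bracket and g, nor can an effect of altered anatomy be isolated within it.

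**Step 3: conditional illustration from the pilot.** The bracket is 55.0 − g:

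| g assumed (min) | D(POST) − D(PRE) (min) |
|---|---|
| 30 | +25 |
| 55 | 0 |
| 90 | −35 |
| 120 | −65 |
| 180 | −125 |

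The range shows that the pilot result is compatible with a positive, zero or negative block-to-bolus difference, depending on a quantity the article does not give.

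**Step 4: why D is not block duration either.** Suppose neither block had any effect, so that both arms asked for a first bolus x minutes after PACU exit. Then D(PRE) = g + e + x and D(POST) = e + x, a difference of −g. The PRE arm gains g minutes under general anaesthesia, when no patient can request a bolus.

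| Scenario | PACU exit to bolus, POST − PRE | Block to bolus, POST − PRE |
|---|---|---|
| Equal block durations, bolus at wear-off | +g | 0 |
| No effect of either block | 0 | −g |

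So neither origin by itself measures how long the block lasts. The Background adds that this block covers somatic and not visceral pain, so a first bolus need not mark the end of the block at all.

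**Step 5: rescue before the clock.** Set the General anaesthesia section beside the Discussion. The former gives titrated opioid before PACU exit; the latter names time to first rescue opioid as an indicator. Time to first PCIA bolus after PACU exit equals time to first rescue only for patients who needed no sufentanil in the PACU.

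**The case against.** The strongest reply is that the interval matches the formal primary objective exactly. The randomised contrast is block timing, so later placement is the intervention and not a bias. A common postoperative start measures the net benefit to the patient, which answers the second Discussion question directly, and the hypothesis can be read in that sense. All of this stands. It would be wrong to say that a positive result shows only that the block was given later: if surgery impaired the POST block enough, the interval would not favour POST.

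A reader might infer from 55.0 − g that the pilot points to a shorter POST block. The documents do not support this. It needs a gap above 55 min when no mean operating time is stated, and equal times to PACU exit. It also subtracts time in which PRE patients could not ask for a bolus. For the same reason, block-to-first-opioid time should not replace the primary as the test of duration, since it favours PRE.

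The sufentanil rule is the same in both arms, a patient with a failed block can still press early after leaving the PACU, and 24-hour oxycodone consumption is a secondary outcome. These points soften the second issue but do not remove it, because the amount of PACU rescue may differ by arm and none of it enters the primary.

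The Data collection section does not list block time or PACU sufentanil. It does not list PACU exit time either, although the primary needs it, so that list is not complete and these omissions are no fault in themselves.

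**Conclusion.** The concern holds as a mismatch between claim and endpoint. The primary interval supports a conclusion about opioid-free time after the PACU under two timing strategies. It cannot answer the first Discussion question, cannot support the Background hypothesis read as intrinsic block duration, and cannot isolate an effect of altered anatomy. If the first bolus marks wear-off and times to PACU exit are equal, the distortion of a duration comparison is about g, which is unknown and limited only by the 180-min removal rule; the pilot difference for comparison is 55.0 min. The size of the uncounted PACU rescue cannot be computed from the article.

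The validity of the randomised comparison is not in question, and no claim about the direction of the true duration difference follows. The table in step 3 of the working is an illustration under stated assumptions only.

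**What to change.** 1. Reword the Background hypothesis and the first Discussion question so that the primary conclusion is limited to postoperative opioid-free time, with no claim about intrinsic block duration or about separating timing from altered anatomy.
2. Add a sensitivity analysis of the primary with the clock started at end of surgery, defined identically in both arms, and PACU sufentanil counted as the first rescue. This needs the time and dose of PACU sufentanil; confirm that the eCRF captures them. It addresses the uncounted rescue, not the duration question.
3. If block-to-first-opioid time is reported, give it as descriptive support only, and state that it favours PRE because no patient-requested opioid can occur under general anaesthesia.

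Fix the wording and the analysis before unblinding. The cost is one extra analysis, at most a few eCRF entries per patient, and a narrower claim. The primary outcome, sample size, visits and treatment are unchanged.

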### Study setting and population

#### Population

Patients scheduled for elective transabdominal gynaecological surgery at the First Hospital of China Medical University will be recruited for the study beginning in September 2015. The purpose, procedures, and potential risks and benefits of the study will be explained to the participants, and written informed consent will be obtained.

#### Inclusion and exclusion criteria

The inclusion criteria are as follows: (1) an age of 18 to 65 years old; (2) scheduled to undergo elective midline incision transabdominal gynaecological surgery for a benign mass; and (3) American Society of Anaesthesiologists (ASA) risk classification I–II.

The exclusion criteria are as follows: (1) patient refusal; (2) known hypersensitivity to the study medication (ropivacaine); (3) long-term use of opioids; (4) liver or renal insufficiency; (5) a history of psychiatric or neurological disease; (6) deafness; (7) previous open surgery; (8) regular use of acetaminophen, nonsteroidal anti-inflammatory drugs, corticosteroids, or antiemetics; and (9) a preoperative Pittsburgh Sleep Quality Index (PSQI) global score of higher than 6 (Fig. 1).

**Fig. 1 Fig1:**
[figure not shown]
Flow chart of the study

#### Ethical aspects and informed consent

The trial was approved by the Ethics Committee of the First Hospital of China Medical University (protocol number 2014071701, Chairman [name]) and was registered with the Clinical Trials Registry (NCT02477098). All of the participants will provide written informed consent in accordance with the Declaration of Helsinki.

